# Critical inspiratory pressure – a new methodology for evaluating and training the inspiratory musculature for recreational cyclists: study protocol for a randomized controlled trial

**DOI:** 10.1186/s13063-019-3353-0

**Published:** 2019-05-07

**Keywords:** Physical exercise, Physiotherapy, Physical performance, Critical power, Respiratory muscle

## Abstract

**Background:**

Inspiratory muscle training (IMT) has brought great benefits in terms of improving physical performance in healthy individuals. However, there is no consensus regarding the best training load, as in most cases the maximal inspiratory pressure (MIP) is used, mainly the intensity of 60% of MIP. Therefore, prescribing an IMT protocol that takes into account inspiratory muscle strength and endurance may bring additional benefits to the commonly used protocols, since respiratory muscles differ from other muscles because of their greater muscular resistance. Thus, IMT using critical inspiratory pressure (PThC) can be an alternative, as the calculation of PThC considers these characteristics. Therefore, the aim of this study is to propose a new IMT protocol to determine the best training load for recreational cyclists.

**Methods:**

Thirty recreational cyclists (between 20 and 40 years old) will be randomized into three groups: sham (SG), PThC (CPG) and 60% of MIP, according to age and aerobic functional capacity. All participants will undergo the following evaluations: pulmonary function test (PFT), respiratory muscle strength test (RMS), cardiopulmonary exercise test (CPET), incremental inspiratory muscle endurance test (iIME) (maximal sustained respiratory pressure for 1 min (PTh_MAX_)) and constant load test (CLT) (95%, 100% and 105% of PTh_MÁX_) using a linear load inspiratory resistor (PowerBreathe K5). The PThC will be calculated from the inspiratory muscle endurance time (T_LIM_) and inspiratory loads of each CLT. The IMT will last 11 weeks (3 times/week and 55 min/session). The session will consist of 5-min warm-up (50% of the training load) and three sets of 15-min breaths (100% of the training load), with a 1-min interval between them. RMS, iIME, CLT and CPET will be performed beforehand, at week 5 and 9 (to adjust the training load) and after training. PFT will be performed before and after training. The data will be analyzed using specific statistical tests (parametric or non-parametric) according to the data distribution and their respective variances. A *p* value <0.05 will be considered statistically significant.

**Discussions:**

It is expected that the results of this study will enable the training performed with PThC to be used by health professionals as a new tool to evaluate and prescribe IMT.

**Trial registration:**

ClinicalTrials.gov, NCT02984189. Registered on 6 December 2016.

**Electronic supplementary material:**

The online version of this article (10.1186/s13063-019-3353-0) contains supplementary material, which is available to authorized users.

## Background

Positive results obtained using inspiratory muscle training (IMT) in active and non-active healthy individuals have transformed this type of intervention into one of the most studied in recent decades [1–3]. IMT, which is already used as an integral part of cardiorespiratory rehabilitation in individuals with respiratory muscle weakness [4–6], is currently an alternative for improving the athletic performance of amateur and professional athletes by reducing the sensation of dyspnea in these individuals [7–15].

However, despite the large number of studies that evaluate the efficiency of IMT, there is a gap in the literature related to choosing the best protocol for each population and training objective. Thus, new studies need to be carried out aimed at establishing the best load (intensity), duration and frequency of training for healthy active individuals and to promote central and peripheral adaptations, which can help regulate respiratory muscle activity [16].

Among these parameters, the most studied is the training load, but there is still no consensus as to which is the best load to use. Thus, respiratory muscle strength (RMS) measurements have mainly been used in published studies and the percentage of maximal inspiratory pressure (MIP) is most commonly used for establishing training loads [16, 17]. However, as well as RMS, respiratory muscle endurance (RME) should also be considered, as together they make up the main characteristics of the respiratory system, and can bring about greater systemic adjustments, leading to an improvement in physical performance as the respiratory muscles stand out from the other muscles due to their great resistance [18].

According to Hajghanbari et al. [3], the loads presented in the studies cited in this review used training intensities between 50% and 80% of MIP. In a review by Janssens et al. [19], the authors concluded that changes in inspiratory muscle strength (IMS) were more significant in training with loads between 60% and 80% of MIP. Thus, most of the studies that show good results after the IMT [3, 19] used the 60% load of MIP. However, to the best of our knowledge, no new methods have been published that use the IMS and inspiratory muscle endurance (IME) together to determine the training load.

Based on this, it was proposed in our group’s previous research to determine the critical inspiratory pressure (PThC) of apparently healthy young and middle-aged men during IME [20]. This new methodology to determine the training load was based on the concept of critical power defined as the limit work (W_LIM_) where an exercise can be maintained for a long period of time (T_LIM_) without any signs of fatigue [21, 22] or as the intensity where the aerobic and anaerobic pathways are recruited together [23].

The determination of PThC is performed by the total work (abscissa) graph for the total time to exhaustion (coordinate), from multiple intensities of exercise to fatigue. Once this is done, a linear regression of the points is performed to identify the curvature constant (W′) and the PThC is determined as the point at which the line intersects the abscissa. This work-time relationship is defined by a hyperbolic function, in which the slope represents the aerobic function and the intercept in y (W′), the anaerobic working capacity, that is, the maximal workload that can be performed using stored energy in the active muscle (adenosine triphosphate, phosphocreatine, glycogen and myoglobin-bound oxygen) [24, 25]. In addition, it should be noted that both IMS and IME are used to determine it; the latter by evaluating PTh_MÁX_, which represents the maximal workload that the individual can sustain for at least 1 min [26–29].

Thus, it was observed that the percentage of PThC is similar to other values of critical power identified in the literature, where PThC and the percentage of PTh_MÁX_ are influenced by age [20]. This suggests that the concept of PThC can be applied as a new IMT tool, as this method considers the characteristics of the respiratory musculature, i.e., IMS and IME together [20].

In addition, during the proposition of a new training load, the results of this new methodology need to be compared with the other loads found in the literature to clarify what the best training intensity is for a given population and to define the responses generated by this training in the main systems involved: the cardiovascular, respiratory and metabolic systems.

IMT using PThC can bring additional benefits, such as increased oxygen uptake (VO_2PEAK_), generated by using a moderate to high intensity load that can be performed over a long period of time [23] due to improving the efficiency of respiratory, cardiovascular and musculoskeletal systems and which will contribute to improved physical performance. In addition, a longer delayed mechanism of inspiratory muscle metaboreflex has been pointed out as one of the main factors responsible for the benefits of IMT in healthy individuals [3, 19].

## Methods

### Aim

The aim of this study is to propose a new methodology to determine the IMT load for recreational cyclists, which promotes better results for physical performance and for cardiovascular, respiratory and metabolic responses compared to traditional methodologies.

#### Primary outcome measures

The primary outcome measure is the performance on exercise: peak oxygen uptake (VO_2PEAK_) and work load (W) were obtained by cardiopulmonary exercise testing (CPET).

#### Secondary outcome measures

The secondary outcome measures are as follows:The cardiovascular responses to IMT: systolic arterial pressure (SAP), dyastolic arterial pressure (DAP), heart rate (HR), cardiac output (CO), stroke volume (SV) and total peripheral vascular resistance (PVR) will be evaluated during the CPET and incremental inspiratory muscle endurance test (iIME).The respiratory responses to IMT: carbon dioxide production (VCO_2_), respiratory exchange rate (RER), respiratory rate (RR), respiratory ventilation (VE), oxygen uptake efficiency slope (OUES) and minute ventilation-carbon dioxide production slope (VE/VCO_2SLOPE_) will be monitored and registered during CPET and iIME. MIP and MEP will be collected in the RMS test. The pulmonary function test (PFT) index comprises: slow and forced vital capacity (SVC and FVC), maximal voluntary ventilation (MVV), forced expiratory volume in 1 s (FEV_1_), relationship between FEV_1_ and CVF (FEV_1_/FVC), IC, expiratory reserve volume (ERV) and MVV.The metabolic responses to IMT: oxyhemoglobin (O_2_Hb), deoxyhemoglobin (HHb) and total hemoglobin (tHb) and VO_2PEAK_ responses will be measured during CPET and iIME.

### Study design

This is an experimental, longitudinal, randomized, controlled and double-blind study. The research participants and the researcher ([name]), who will perform the evaluation and reevaluation protocols and statistical analysis, will be blinded. The researcher who will carry out the study analyses (tabulation, data processing and statistical analyses) will not participate in the randomization and training of the participants. Thus, after tabulating all the data, the same person ([name]) will receive a table of data from the other researchers, separated by training groups, using codes to perform the statistical analysis. The participants will be blinded to the training loads to which they are being submitted, by means of a barrier fixed on the computer screen. The methodological design was based on the Standard Protocol Items: Recommendations for Interventional Trials (SPIRIT) (Additional file 1) [30].

### Subjects

Thirty recreational male cyclists, aged between 20 and 40 years, will be evaluated. They will be randomly divided into three groups: sham group (SG), PThC group (CPG) and 60% of the MIP group (60G). The groups will be formed by the randomization of the paired individuals with the same aerobic functional classification [31] and age group (subdivided into decades), using R software 3.0.2 to allocate the subjects.

The criteria used to select the participants will be as follows: male subjects aged 20 to 40 years old, apparently healthy, who have been practicing cycling for at least 6 consecutive months and at least 150 min/week (classified as active by the American College of Sports Medicine [32]). In addition, participants must not have abnormalities in the cardiovascular, respiratory, musculoskeletal or neurological systems, nor of other systems that make the proposed tests impossible. The exclusion criteria of the study are as follows: participants with electrocardiogram (ECG) changes (ischemia, overload, severe arrhythmias (such as ventricular tachycardia) and conduction disorders), both at rest and during the clinical exercise test, obesity (body mass index (BMI) >30 kg/m^2^), diabetes mellitus, hypertension, alterations in the results of laboratory tests, participants with respiratory muscle weakness (MIP<60% predicted [33]), smokers or former smokers with at least 1 year of interruption, alcoholics and users of illicit drugs or medication that may interfere with the results of the research and participants who have performed some type of IMT the last 12 months.

The participants will be recruited by electronic and printed media and by contact with subjects included in the database of the Laboratory of Cardiovascular Physiotherapy (LFCV) at the Federal University of São Carlos (UFSCar). Once identified, eligible participants will be invited to participate in the study and after they have accepted, they will carry out all the evaluations described subsequently and the type of training to which they are allocated.

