#### Statistical analysis

Due to the lack of studies that evaluate the effect of different loads of IMT, among them PThC, on the physical performance in recreational cyclists, we chose to carry out the statistical analysis considering the desired study effect size as proposed by Cohen [48]. Thus, the sample calculation was performed using GPower software 3.1.3 to determine the sample size, the mean effect size (*f* = 0.25, according to Cohen [48]) was used for the two-way mixed analysis of variance (ANOVA) and values of 0.05 for the type I probability error (α) and 0.80 for the type II probability error (power or β). Therefore, in order to ensure these pre-established conditions, at least 30 subjects should participate in this study.

All statistical analyses will be processed using the SPSS Statistics software 17.0 (SPSS Inc., Chicago, IL, USA). The level of significance will be set at *p* < 0.05. Normally distributed data will be presented according to the mean ± standard deviation and non-normally distributed data according to the median (interquartile range).

The Shapiro-Wilk test will be used to test for normal distribution and the Levene test for evaluation of homogeneity. A descriptive analysis of the three groups evaluated and then the paired *t* test will be performed on the following data: age, anthropometric evaluation, body composition densitometric analysis and blood test results.

The three groups will be compared considering the factors of group and training time, in terms of the variables PFT (FVC, FEV_1_/FVC, IC, ERV and MVV), RMS (MIP and MEP), CPET (VO_2PEAK_, VE, RR, OUES and VE/VCO_2_slope), cardiovascular variables (HR, CO, SAP, SV, total PVR) and metabolic variables (O_2_Hb, HHb, tHb and VO_2PEAK_), using two-way mixed ANOVA for parametric data analysis and for non-parametric data analsysis, the data will be mathematically transformed in order to normalize the data.

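### Allocation is matched on aerobic class and age decade but the ANOVA has only group and time, so group main-effect and single-visit tests are conservative; group × time is affected only if those factors predict change

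*Protocol article*

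**What the plan says.** On allocation, the Subjects section states: "They will be randomly divided into three groups: sham group (SG), PThC group (CPG) and 60% of the MIP group (60G"). It adds that the groups will be "formed by the randomization of the paired individuals with the same aerobic functional classification [31] and age group (subdivided into decades"). The Methods paragraph of the abstract agrees that randomisation is "according to age and aerobic functional capacity".

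On analysis, the Statistical analysis section states: "The three groups will be compared considering the factors of group and training time", "using two-way mixed ANOVA for parametric data analysis". It lists the outcomes to which this applies, VO2peak among them. It names no stratum, block or covariate.

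On sample size, the same section says that "the mean effect size (*f* = 0.25, according to Cohen [48]) was used for the two-way mixed analysis of variance (ANOVA"), with "values of 0.05 for the type I probability error (α) and 0.80 for the type II probability error (power or β"), and arrives at 30 participants. The Experimental protocol section places the CPET, which gives the primary outcomes, at weeks 1, 5, 9 and 13. The Expected results section anticipates that the PThC arm will gain more in workload and VO2peak than the other two arms.

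**The concern.** Matching before randomisation makes the arms more alike on the matched factors than independent samples would be. Variance due to those factors then no longer contributes to the difference between arms. A model without the factors still counts that variance as error, so the reported standard error exceeds the true one and the test rejects too seldom.

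Aerobic functional class is closely tied to VO2peak, a primary outcome, so the share involved could be material. With about 10 participants per arm there is little precision to spare. The Statistical analysis section does not leave the factor list open: it fixes group and training time, and that list does not match the allocation.

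The right error term also cannot be read from the text, because it speaks of pairing where there are three groups. That could mean matched triplets or strata.

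**Working it through.** **Inputs from the article:** 3 groups, N = 30, CPET at 4 visits (m = 4), f = 0.25, α = 0.05, power 0.80.

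**Assumed, because not stated:** equal allocation (10 per arm), visit correlation ρ = 0.5, sphericity, total SD = 1, and the shares of variance explained by the matching factors.

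**1. Which test does N = 30 belong to?** For the group × time interaction the noncentrality is λ = f²·N·m/(1 − ρ) = 0.0625 × 30 × 4/0.5 = 15, with df = (3 − 1)(4 − 1) = 6 and (30 − 3)(4 − 1) = 81. Power is 0.809 and the smallest N reaching 0.80 is 30, so the stated figure reproduces. For the group main effect, λ = f²·N·m/(1 + 3ρ) = 0.0625 × 30 × 4/2.5 = 3, with df 2 and 27. Power is 0.29, and 102 participants (a multiple of three) would be needed. Some other settings also return 30: the interaction with 3 visits and ρ = 0.6, and the time effect with 2 visits and ρ = 0.6 or 3 visits and ρ = 0.5. No setting tried for the group main effect (2 to 4 visits, ρ from 0 to 0.9) gave fewer than 42.

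**2. Group main effect (mean over four visits).** Split each participant's variance into a stable part ρ and a within-subject part 1 − ρ. Let R² be the share of the stable part explained by the matching factors.
- Variance used by the planned model: ρ + (1 − ρ)/4 = 0.5 + 0.125 = 0.625. SE of a pairwise difference = √(2/10 × 0.625) = 0.354.
- Variance relevant under matching: ρ(1 − R²) + (1 − ρ)/4.

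| R² | Relevant variance | SE with factors fitted | Unadjusted SE too large by |
|---|---|---|---|
| 0 | 0.625 | 0.354 | 0% |
| 0.2 | 0.525 | 0.324 | 9% |
| 0.4 | 0.425 | 0.292 | 21% |
| 0.6 | 0.325 | 0.255 | 39% |

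The same formula gives 7%, 16% and 27% at ρ = 0.3, and 10%, 25% and 48% at ρ = 0.7. In simulation with matched triplets and ρ = 0.5, the true type I error of the unadjusted main-effect test was 3.1%, 1.6% and 0.7% for R² = 0.2, 0.4 and 0.6.

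**3. Comparison at one visit.** The variance is 1 unadjusted and 1 − ρR² under matching, that is 0.9, 0.8 and 0.7. The unadjusted SE is too large by √(1/0.9) − 1 = 5%, √(1/0.8) − 1 = 12% and √(1/0.7) − 1 = 20%.

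**4. Group × time, matching factors related to level only.** In a change score the stable part cancels. The variance of the change from first to last visit is 2(1 − ρ) = 1, and the SE of a difference between arms is √(2/10 × 1) = 0.447, with or without the matching factors and whatever R² is. Simulated type I error of the unadjusted interaction test was 5.4%, 5.2% and 5.2% at ρ = 0.5 with R² = 0.3, 0.5 and 0.7, which is close to nominal.

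**5. Group × time, matching factors related to the change.** If they explain a share Rc of change variance, the unadjusted SE is too large by 1/√(1 − Rc) − 1. Power below uses λ = 15/(1 − Rc). Error df are (27 − 3) × 3 = 72 for an assumed four strata, and (27 − 9) × 3 = 54 for ten triplets, with terms by time fitted.

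| Rc | SE too large by | Power, strata fitted | Power, triplets fitted |
|---|---|---|---|
| 0 | 0% | 0.805 | 0.791 |
| 0.1 | 5% | 0.851 | 0.839 |
| 0.2 | 12% | 0.896 | 0.886 |
| 0.3 | 20% | 0.936 | 0.928 |

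The planned figure for comparison is 0.809.

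**The case against.** The strongest reply is that the trial relies on group × time. The hypothesis concerns a greater gain, the sample size reproduces for the interaction, and baseline is already a level of the time factor. In that test stable fitness and age differences cancel, so omitting the matching factors costs nothing unless they predict the response to training. No passage says that they do. Adding them as main effects alone would not touch the interaction's error term, and adding them by time when they predict nothing loses a little power. The shares used above are also assumed. Participants are all male, active and aged 20 to 40, so age in decades is a coarse factor with a narrow range. The error is in any case on the safe side.

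Most of this stands, and it limits the point. A reader might infer that every between-group test is badly weakened. Simulating one week-13 comparison in ten matched sets without baseline does give a true type I error of 1.8%, 0.6% and 0.1% when matching explains 30%, 50% and 70% of outcome variance. Power for one arm 0.8 SD better is then 36%, 33% and 29%, against 52%, 67% and 88% with the sets fitted. The article does not support carrying those figures over, because it plans a mixed ANOVA over repeated visits and not a single-visit test.

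The objection does not remove the mismatch. The Statistical analysis section never names the interaction as the only or primary test. It lists group as a factor, so the group effect will be computed and may be reported.

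**Conclusion.** The analysis as stated does not reflect the allocation as stated. The consequence is a conservative, unbiased loss of precision, and type I error is not inflated. For the group main effect the standard error is about 9% to 39% too large, if matching explains 20% to 60% of stable between-subject variance and visits correlate at 0.5. Single-visit comparisons lose less on the same assumptions, about 5% to 20%. The group × time interaction is unaffected by stable differences; it loses about 5% to 20% on the standard error only if aerobic class or age decade explains 10% to 30% of the change variance. None of these shares can be derived from the article, so the ranges show how large the loss could be and are not estimates. This is a modest point, worth making because the correction is cheap.

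**What to change.** In the Statistical analysis section, state whether allocation used strata or matched triplets. Then add the matching terms to each between-group model: age decade and aerobic functional class as fixed factors if strata were used, or the set as a block if triplets were used. Include their interaction with time where they are expected to predict change, since main effects alone do nothing for group × time. Merge sparse aerobic classes by a rule fixed before unblinding.

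Both factors are known before allocation, so no new data are needed. The cost is a few between-subject error degrees of freedom with strata (3 of 27 for the assumed four strata), or 9 of 27 with triplets. If the factors turn out not to predict change, interaction power falls from 0.809 to 0.805 with strata (0.4 percentage points) or to 0.791 with triplets (about 2 points).

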### Study planning

The present study will be conducted in accordance with the Helsinki Declaration. This study was approved by the Human Research Ethics Committee at the Federal University of São Carlos (UFSCar) (number 1.558.731). All subjects will provide signed informed consent.

The experimental tests and procedures will be performed at the LFCV at the Nucleus of Research in Physical Exercise (NUPEF) at the Department of Physical Therapy (DFisio) and the clinical ergometric tests at the Cardiovascular Physiotherapy area of the School Health Unit (USE), both located at UFSCar, São Carlos campus. The blood tests will be performed at the Clinical Analysis Laboratory at UNIMED (a cooperative medical system) in São Carlos (UNILAB).

Environmental conditions will be controlled, and participants will be instructed according to Perseguini et al. [34]. The tests will always be performed in the afternoon, considering the influence of the circadian cycle on the evaluation results.

On the day of the tests, previously to applying the experimental protocols, the conditions related to the participants’ state of health will be observed. Moreover, prior to the tests, participants will be familiarized with the equipment, respiratory maneuvers and the subjective perception of effort scale – BORG/CR10 [35] in order to reduce participants’ anxiety and prevent the effect of the learning process from affecting the search results.

